### Procedure for unblinding if needed {17b}

To maintain trial integrity, blinded trial personnel will only be unblinded in exceptional circumstances (for example, when knowledge of the actual treatment received is essential for further management of the participant). Requests for unblinding will be considered by the chief investigator, where practical, in consultation with the chair of the DSMB. Unblinding will be recorded and reported as a deviation from protocol and will not result in study discontinuation.

## Data collection and management

### Plans for assessment and collection of outcomes {18a}

Study outcomes, measures (including references for reliability and validity), and timing of assessment are outlined in Outcomes {12}. Screening and demographic data will be entered by participants and trained research staff into REDCap. All outcome data, except for the CRPS severity score which requires input from a clinician, will be entered directly into REDCap by participants. Should outcome data be obtained via telephone, it will be entered into REDCap by a research assistant and checked by another staff member.

### Plans to promote participant retention and complete follow-up {18b}

Participant retention will be optimised through regular participant contact and check-in telephone calls. The importance of completing follow-up assessments will be emphasised. Automated email reminders will be sent via REDCap if outcome assessments are not completed within 24 h of their delivery. If outcome measures remain incomplete following reminders, the study team will contact participants via SMS or telephone.

Participants have the right to withdraw from the study at any time. Where possible, a reason for withdrawal will be recorded. If participants express that they wish to discontinue the trial treatment(s), the study team will ascertain whether the participant is willing to continue to complete outcome assessments. If participants wish to withdraw from future outcome assessments, all data collected up until the moment of withdrawal will be retained unless objections are made by the participant.

### Data management {19}

All participant data, except for MBS/PBS data, will be collected, managed, and stored on the web-based REDCap platform. REDCap uses intuitive electronic case report forms, pre-defined fields, and real-time data validation and integrity checks to ensure data consistency and quality. REDCap provides encryption between the data entry client and the server and individual access to the database via secure login with 2-factor authentication. The REDCap database will only be accessible by approved research staff.

The REDCap application and data will be housed on a server managed by the University of New South Wales Sydney. The database is securely backed up as per standard University of New South Wales procedures for data security. For the purpose of specialised autoscoring and functionality of the PROMIS computerised adaptive testing, REDCap communicates with Vanderbilt University’s server (Nashville, TN, USA). The security of this server is ensured, and no personally identifiable information is sent to the server. Participants are informed of this requirement before they provide informed consent.

The MEMOIR study data will be archived for 15 years, consistent with clinical trial recommendations outlined in the National Health and Medical Research Council’s ‘Australian Code for the Responsible Conduct of Research’, after which electronic information will be permanently deleted.

### Confidentiality {27}

All participants will be provided with an identification number. All data will be coded with this number so that any data collected will only be identifiable by the code. All analyses will be done using de-identified data. Results will be disseminated using aggregate data to ensure confidentiality is preserved.

### Plans for collection, laboratory evaluation, and storage of biological specimens for genetic or molecular analysis in this trial/future use {33}

Biological specimens will not be collected in this study.

## Statistical methods

### General analysis principles

The primary objective of the trial is to estimate the effects of memantine compared to placebo memantine and graded motor imagery compared to no graded motor imagery on pain intensity and pain interference. Consequently, the focus of the analysis and the interpretation of the trial findings will be on the magnitude of point estimates of effects and the precision of those estimates, quantified with confidence intervals. The analysis will be supplemented by *p* values but not by claims about statistical significance or non-significance [57].

Preliminary, blinded analyses will be conducted before the final analysis. The preliminary analyses will be conducted using randomly permuted ‘dummy’ treatment allocations. These analyses will identify any issues with the analysis pipeline and enable decisions to be made about, for example, distributional assumptions, without knowledge of the implications of those decisions on the trial’s findings. Once those issues have been resolved and the statistical code has been finalised, the definitive analysis will be conducted using true allocations. Analyses will be performed using R and Stata software.

### Descriptive analysis

A Consolidated Standards of Reporting Trial (CONSORT) diagram will be used to summarise the participant flow through the MEMOIR trial [58] (Supplementary Fig. 2). The diagram will show the number of participants assessed for eligibility and excluded (with reasons), and for each comparison, the number randomised, allocated to (and received) interventions, discontinued interventions (with reasons), lost to follow-up for the dual primary outcomes (for each timepoint), analysed in the primary analysis, and excluded from analysis (with reasons).

Baseline demographic and clinical data will be presented to characterise the study sample. Counts and percentages will be presented for binary and categorical variables. Means and standard deviations or medians and interquartile ranges will be presented for continuous variables. The following characteristics will be described, grouped as per the main comparisons (memantine versus placebo, graded motor imagery versus no graded motor imagery) (see Supplementary Table 1):AgeSexBody mass indexSmoker statusWeekly alcohol consumptionEthnicityAboriginal or Torres Strait IslanderGeographical remotenessIndex of relative socioeconomic advantage and disadvantageWork statusEducation levelCRPS durationInciting eventPrimary CRPS locationLimb dominance before CRPSCompensability of CRPSPrescription medicine useOver-the-counter-medicine useCRPS healthcare visits

### Statistical methods for primary and secondary outcomes {20a}

#### Main analysis

All outcomes will be analysed according to the intention to treat principle. The analysis will involve estimation of the marginal mean effect of memantine compared to placebo and the marginal mean effect of graded motor imagery compared to no graded motor imagery on pain intensity and pain interference at 16 weeks. Additional information on the estimands of interest, including handling of intercurrent events, is provided in Table 2. As the trial has dual primary outcomes, interval estimates will be 97.5% confidence intervals. There will be no multiplicity adjustment for the two interventions as the factorial design answers two distinct questions.

**Table 2 Tab2:** Trial estimands

Estimand component	Definition
Interventions to be compared	To estimate the average causal effect of memantine, we will compare the mean outcome of trial participants allocated to receive memantine and graded motor imagery or memantine only with the mean outcome of trial participants allocated to receive placebo and graded motor imagery or placebo only To estimate the average causal effect of graded motor imagery, we will compare the mean outcome of trial participants allocated to receive memantine and graded motor imagery or placebo and graded motor imagery with the mean outcome of participants allocated to receive memantine only or placebo only
Population of interest	Adults with CRPS as defined by the trial eligibility criteria
Outcome of interest	Pain intensity, measured on a 11-point NRS; pain interference, measured with PROMIS pain interference v1.1
Summary measure (population-level)	Mean difference
Intercurrent events	All intercurrent events relating to memantine and graded motor imagery (e.g. intervention discontinuation, use of non-trial treatments) will be handled using a treatment policy strategy

For each of the dual primary outcomes, we will fit a longitudinal mixed-effects model that includes terms for the fixed effects of each intervention, the three follow-up timepoints, the intervention by time interactions, the two-way interaction between the interventions, and the baseline values of the outcome variables. In addition, the models will include terms for the fixed effects of the duration of CRPS (modelled as linear or linear with log transformation) and workplace compensation status, as well as random intercepts for trial participants.

The coefficients in the model are conditional on the other factors in the model. However, our primary interest is in the estimation of the marginal effects of the interventions. Point and interval estimates of the marginal effect of each intervention at 16 weeks will be obtained by appropriately weighting the sum of the relevant model coefficients and the elements of the variance-covariance matrix using the -margins- command in Stata. Secondary outcomes and safety outcomes (the number of participants experiencing at least one adverse event, specific adverse events, serious adverse events) will be analysed in the same way except that log binary models will be used for binary outcomes. For each comparison, mean differences or risk ratios, each with 97.5% confidence intervals, will be presented in tables (see Supplementary Tables 2, 3, 4, and 5).

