#### Primary outcomes

The dual primary outcomes are pain intensity and pain interference. These outcomes were selected by the study consumer panel as they were determined to represent the most important aspects of improvement for CRPS. Pain intensity is the average pain intensity of the affected limb over the previous 7 days assessed using the 11-point numeric rating scale (NRS) [38], with scores of 0 indicating ‘no pain’ and scores of 10 indicating ‘worst imaginable pain’. This scale has demonstrated validity and reliability for use in chronic pain research [39]. Pain interference is assessed using the Patient-Reported Outcomes Measurement Information System (PROMIS) Pain Interference v1.1 [40], measured over the previous 7 days, with higher scores indicating greater pain interference. This measure has demonstrated reliability and validity across different pain populations [40, 41]. Both dual primary outcomes will be assessed as differences in mean final values at 16 weeks post-randomisation.

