#### Secondary outcomes

Pain intensity, assessed over the previous 7 days using the 11-point NRS. Collected at 26 and 52 weeks post-randomisation.Pain interference, assessed over the previous 7 days using PROMIS Pain Interference v1.1. Collected at 26 and 52 weeks post-randomisation.Physical function, assessed at present using PROMIS Physical Function v2.0 [42], with higher scores indicating greater physical function. Collected at 16, 26, and 52 weeks post-randomisation.Fatigue, assessed over the previous 7 days using PROMIS Fatigue v1.0 [43], with higher scores indicating greater fatigue. Collected at 16, 26, and 52 weeks post-randomisation.Self-efficacy to manage symptoms, assessed at present using PROMIS Self-Efficacy Manage Symptoms v1.0 [44], with higher scores indicating greater self-efficacy to manage symptoms. Collected at 16, 26, and 52 weeks post-randomisation.Cognitive function, assessed over the previous 7 days using PROMIS Cognitive Function Abilities Subset v2.0 [45], with higher scores indicating greater cognitive function. Collected at 16, 26, and 52 weeks post-randomisation.Depressive symptoms, assessed over the previous 7 days using PROMIS Depression v1.0 [46], with higher scores indicating greater depressive symptoms. Collected at 16, 26, and 52 weeks post-randomisation.Health-related quality of life, assessed over the previous 7 days and ‘generally’ using PROMIS Global Health short form v1.1 [47], with higher scores indicating better health-related quality of life. Collected at 16 and 52 weeks post-randomisation.Pain self-efficacy, assessed at present using Pain Self-Efficacy Questionnaire (two-item short form) (PSEQ-2) [48]. The PSEQ-2 comprises two 7-point Likert scales (total score = 14), with higher scores indicating higher pain self-efficacy. Collected at 16, 26, and 52 weeks post-randomisation.Patient Global Impression of Change [37], assessed at present using a 7-point scale, with higher scores indicating greater improvements. Collected at 16 weeks post-randomisation.CRPS severity, assessed at present using the CRPS Severity Score [49, 50]. The CRPS Severity Score assesses 8 self-report symptoms and 8 clinician-assessed signs (total score = 16), with higher scores indicating greater CRPS severity. Collected at 16 weeks post-randomisation.Cost effectiveness, assessed as prescription and over-the-counter medicines use and visits (yes/no) to a healthcare provider for CRPS. Collected via self-report questionnaires and MBS and PBS data at 16, 26, and 52 weeks post-randomisation.Adverse events, assessed as the number of participants with at least one adverse event, serious adverse event, or specific adverse event (yes/no). Collected during treatment and during follow-up.

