
Continuous outcomes will be assessed as differences in mean final values at each timepoint; binary outcomes will be assessed as ratios of proportions.

PROMIS instruments use a *T*-score metric, in which 50 is the mean of the reference population and 10 is the standard deviation of that population [51]. All PROMIS scales, except for Global Health short form v1.1, will be measured using computer adaptive tests. Computer adaptive tests use item response theory to provide precise measurement using few items, and allow for scores that are directly comparable across different selections of items [52].

Pain intensity, pain interference, physical function, self-efficacy, and cognitive function will also be measured at 12 weeks to explore the mechanisms by which the graded motor imagery intervention exerts its effects. To evaluate the effect of adhering to the interventions, the following outcomes will also be measured: weekly measures of pain intensity, item 4 of the Credibility/Expectancy Questionnaire [53], Medical Form Confidence (weekly); International Physical Activity Questionnaire Short Form [54] (end of treatment only). See Methods for additional analyses (e.g. subgroup analyses) {20b} for further information.

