### Methods in analysis to handle protocol non-adherence and any statistical methods to handle missing data {20c}

The analyses are based on the intention-to-treat principle, where all participants will be assessed in the groups to which they are randomised, regardless of the intervention received or intervention adherence. A summary of the interventions allocated and received will be reported for each comparison. Details on the presentation of intervention adherence and protocol deviations are provided in Appendices 1 and 2 and Supplementary Tables 7 and 8.

Efforts will be taken to minimise the amount of missing outcome data (see Plans to promote participant retention and complete follow-up {18b}). For each outcome, the amount of missing data will be reported. The nature and pattern of data missingness will be explored to determine, as far as is possible, whether data can be treated as missing completely at random (MCAR) or missing at random (MAR). If more than 10% of the primary outcome data are missing and the MAR assumption appears plausible, a sensitivity analysis will be conducted in which the main analysis is replicated using multiple imputation [65, 66].

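### The primary model leaves out the week-12 scores of both primary outcomes, so a participant lost for good between weeks 12 and 16 adds nothing and the week-16 effect can be modestly biased

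*Protocol article*

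**What the plan says.** The Main analysis section ({20a}) gives each primary outcome a longitudinal model with "terms for the fixed effects of each intervention, the three follow-up timepoints, the intervention by time interactions". Baseline enters this model as a covariate, not as an outcome row, alongside two further covariates and "random intercepts for trial participants".

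That section does not name the three visits, but the outcome sections leave one natural reading. The dual primary outcomes are compared at 16 weeks after randomisation. For the later visits, the list of secondary endpoints has this entry for pain: "Pain intensity, assessed over the previous 7 days using the 11-point NRS. Collected at 26 and 52 weeks post-randomisation". Pain interference has the same weeks.

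The end of the outcomes section adds that pain intensity and pain interference, among others, "will also be measured at 12 weeks to explore the mechanisms by which the graded motor imagery intervention exerts its effects". It also lists "weekly measures of pain intensity" for the adherence work. Nothing in the article brings either set of scores into the week-16 estimate.

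For missing data, section {20c} says that if more than 10% of primary outcome data are missing and MAR seems plausible, "a sensitivity analysis will be conducted in which the main analysis is replicated using multiple imputation". It lists no imputation variables.

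**The concern.** With baseline on the right-hand side, a participant enters the likelihood only through values at weeks 16, 26 or 52. Someone who leaves for good in week 13 because pain is uncontrolled has a week-12 score on both primary outcomes, yet has no row. For such leavers the model needs missingness to be random given baseline and the other covariates. If leaving depends on recent pain, that fails, although the recorded week-12 score would have made a weaker assumption enough.

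Reasons for leaving can differ by arm, and graded motor imagery is unblinded. The General analysis principles put interpretation on the size of the point estimates, and the Sample size section judges them against 1 NRS point and 5 T-score points. A small shift in the estimate therefore touches what the trial will report.

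**Working it through.** **Inputs from the article.** Sample size {14}: difference 1 point with SD 2 (pain), 5 with SD 10 (interference), adjacent correlation 0.7, 182 evaluable, 10% dropout, 204 recruited. Visits and model terms are as described above.

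**The plan's own figures.** 182 × 1.1 = 200.2, raised to 204. At 10% loss, 204 × 0.10 ≈ 20 participants are lost and 204 × 0.90 ≈ 184 remain. The 182 is approached as follows:
- Unadjusted total: 4 × (2.241 + 1.282)² × 2²/1² ≈ 198.6.
- Times 1 − 0.343² (correlation 0.7³) gives about 175, or 178 with a t correction.

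The article does not name the correlation structure or contrast, so this match rests on one reading. The present point does not depend on it.

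**Mechanism.** Let f be the fraction lost in an arm, D the leavers' mean excess in baseline-adjusted week-12 pain, and b the slope of week 16 on week 12 given baseline. Stayers' week-16 mean is then too low by about b × f/(1 − f) × D.
- First-order autoregressive, 0.7 between neighbouring visits: b = (0.7 − 0.7 × 0.49)/(1 − 0.49) = 0.70.
- Exchangeable, 0.7 throughout: b = (0.7 − 0.49)/(1 − 0.49) = 0.41.
- With f = 0.10, f/(1 − f) = 0.111. For an assumed D of 0.5 to 1.5 points, the shift is 0.70 × 0.111 × D = 0.04 to 0.12, or 0.41 × 0.111 × D = 0.02 to 0.07.

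The bias in the effect is the difference between the two arms' shifts. If both arms lose people by the same rule and there is no true effect, the shifts cancel. Under decaying correlation, a single baseline coefficient for all visits adds a little more, because baseline then predicts each later visit less well.

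**Simulation.** True effect −1.0, SD 2, both correlation structures, logistic loss on week-12 pain, 10% loss, all after week 12:

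| Loss rule | Week-16 estimate, planned model | Bias, % of 1 point |
|---|---|---|
| Same rule in both arms | −0.94 to −0.99 | 1-6 |
| Pain-driven in one arm, random in the other | −0.87 to −0.96 | 4-13 |

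Adding a week-12 row with an unstructured covariance brings the bias to about zero. With the planned random intercept alone, up to about 0.03 can remain under the autoregressive structure.

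**Timing of loss.** Under the one-arm rule, with earlier loss taken as random, the planned model gives −0.94 to −0.98 if half of the 10% falls after week 12. If a quarter does (an even spread over 16 weeks), it gives −0.97 to −0.99.

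**Scale.** The standard error at week 16 with 184 analysed is 2 × √(1 − r²) × √(4/184): 0.257 for r = 0.49 and 0.211 for r = 0.7. The largest bias in the table arises under the autoregressive structure (r = 0.49): 0.13/0.257 ≈ 0.5 standard errors.

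**Pain interference.** The standardised effect is the same (1/2 = 5/10). If loss depends on week-12 interference to the same degree per SD, the percentages carry over: 1-6% of 5 is 0.05 to 0.3 T-score points, and 4-13% is 0.2 to 0.65.

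**The case against.** The strongest reply is that nothing here is contradictory. Weeks 16, 26 and 52 match the stated objectives, week 12 has its own stated purpose, and the problem is small. Most of this stands.

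- **Loss before week 12.** The 10% dropout is not tied to weeks 12-16. Titration fills the first four weeks, and someone lost then has no week-12 score to use. A reader might take 4-13% as the bias expected at the planned dropout. It is the result when all loss comes late and follows pain in one arm only.
- **Stopping treatment is not loss.** Section {18b} seeks continued outcome assessment from those who stop, and the treatment policy strategy keeps their data. Many reasons for quitting treatment therefore produce no missing value.
- **Missing week 16 is not the same as contributing nothing.** A participant who returns at week 26 or 52 still has a row. Only permanent loss removes someone.
- **Imputation.** A reader might infer that section {20c} shuts out the week-12 and weekly scores. It does not. Replicating the main analysis fixes the analysis model, and the choice of imputation variables is ordinary detail left open. That section contains no error on this point.
- **Group coverage.** Table 1 is not shown, so week-12 measurement in all four groups is inferred. The text states no restriction, and a mediation analysis of graded motor imagery needs both of its arms.

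What remains is a stated model choice that sets aside collected scores which would help with late loss.

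**Conclusion.** The point holds as a worthwhile, inexpensive improvement. It is not a flaw that undermines the trial. At 10% loss falling wholly after week 12 and driven by week-12 pain, the week-16 effect is biased by about 1-6% of a 1-point effect under a common rule and about 4-13% under a one-arm rule. In these cases that is at most about half a standard error. The bias shrinks with earlier loss and with successful follow-up after stopping treatment, and is nil under a common rule with no true effect.

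The loss rules, their strength, the timing of loss and the correlation structure are assumptions. Rules running in opposite directions in the two arms would add their biases and could exceed this range, but the article gives no reason to plan for that. Nor does it support saying that a week-12 row always removes the bias: this requires loss to depend on what has been recorded by week 12, and a covariance that lets week 12 inform week 16 properly.

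**What to change.** In the Main analysis section:
1. Name the visits, and add week 12 as a fourth outcome timepoint for both primary outcomes.
2. Keep the marginal contrast at week 16 as the primary estimate, so the estimand in Table 2 is unchanged.
3. Allow a covariance less restrictive than a random intercept, for example unstructured across the four visits, and add baseline-by-time terms.

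As an optional addition, name the week-12 scores and the weekly pain scores as auxiliary variables if multiple imputation is run. The weekly scores are the only ones that help for people lost before week 12. The article describes weekly collection for pain intensity only, so this does not directly cover pain interference.

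The cost is a few more parameters and a change of wording, with no new data collection. The final assessment is expected in Q2 2027 and the code is to be settled on dummy allocations first, so the change can be made before true allocations are used.

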### Methods for additional analyses (e.g. subgroup analyses) {20b}

#### Sensitivity analyses

Sensitivity analyses will be conducted to assess the impact of deviations to the ‘no interaction’ assumption on the primary outcomes. As recommended by Kahan et al. [59], the size, confidence intervals, and *p* value of the treatment-by-treatment interaction will be inspected to assess the plausibility of the assumption of no interaction underpinning the interpretation of the marginal estimator. Further sensitivity analyses will be conducted on the primary outcomes to estimate the effects of each intervention conditional on the presence or absence of the other intervention, again using the -margins- command in Stata. The effect of each intervention combination (memantine and graded motor imagery; memantine only; graded motor imagery and placebo) compared with the double control group (placebo only) will also be estimated (Supplementary Table 6). Multi-arm analyses remain unbiased even when interventions interact [59].

The analyses described below may be reported in secondary publications.

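### The primary model holds the memantine-by-imagery interaction constant over 16, 26 and 52 weeks, so the planned interaction check and the week-16 conditional effects are off if that interaction changes after treatment

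*Protocol article*

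**What the plan says.** The Main analysis section specifies, for each primary outcome, a longitudinal mixed model with "terms for the fixed effects of each intervention, the three follow-up timepoints", then "the intervention by time interactions, the two-way interaction between the interventions, and the baseline values of the outcome variables", two further covariates, "as well as random intercepts for trial participants". The three timepoints are read here as 16, 26 and 52 weeks: the primary assessment is at week 16, and the Secondary outcomes section adds both primary measures "Collected at 26 and 52 weeks post-randomisation". The week-12 measurement is described separately, as exploratory work on mechanisms.

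The primary result is a week-16 quantity: "Point and interval estimates of the marginal effect of each intervention at 16 weeks will be obtained by appropriately weighting" the model coefficients, with Stata's margins command.

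The Sensitivity analyses section uses the interaction in three ways:

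- It inspects the interaction's size, confidence interval and p value, to judge whether assuming no interaction is plausible.
- It uses margins again "to estimate the effects of each intervention conditional on the presence or absence of the other intervention".
- It compares each of the three active combinations with the double control group, and adds that "Multi-arm analyses remain unbiased even when interventions interact". No model is named for these contrasts.

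**The concern.** The listed interaction between the interventions is two-way only; no term lets it vary with time. Each main effect may rise or fade over follow-up while the interaction may not. These choices sit badly together: if both effects may change once treatment ends at 16 weeks, there is no evident reason for their interaction on the absolute scale to stay fixed.

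The Sensitivity analyses section is where the plan tests the assumption behind its factorial design. The primary question is at week 16, but the inspected coefficient also draws on two timepoints after the treatment period. A week-16 interaction that later fades would look smaller than it is; one that grows would look larger. The blinded preliminary analyses cannot reveal this, because randomly permuted allocations remove any real interaction.

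**Working it through.** **Inputs from the protocol article.** Allocation 1:1:1:1; three timepoints; random intercepts; N = 182 evaluable; SD 2 NRS points; target difference 1 point; correlation 0.7 between adjacent timepoints; 97.5% intervals. The plan gives no figure for the interaction, so there is none to reproduce. The 182 is used only for standard errors.

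**Assumption, not in the documents.** The size of the interaction at each timepoint.

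**Formulas.** Let I16 be the true week-16 interaction and Ibar the mean of the interactions at weeks 16, 26 and 52. With balanced, complete data and a random intercept:

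- The fitted interaction equals Ibar, so its error is Ibar − I16.
- The week-16 marginal effects, M (memantine) and G (imagery), are estimated without bias, because intervention-by-time terms are in the model.
- Memantine without imagery is M − I16/2 and is fitted as M − Ibar/2. The error is (I16 − Ibar)/2. With imagery the error has the same size and opposite sign. The same holds for imagery without and with memantine.
- Combination versus double control is M + G. The interaction cancels, so there is no error.

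**Numbers (NRS points).**

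| Assumed interaction, weeks 16/26/52 | Fitted interaction | True at week 16 | Size of error in conditional effects |
|---|---|---|---|
| 1/0/0 | 1/3 = 0.33 | 1 | (1 − 0.33)/2 = 0.33 |
| 1/0.5/0 | 1.5/3 = 0.50 | 1 | (1 − 0.50)/2 = 0.25 |
| 0.5/0.25/0 | 0.75/3 = 0.25 | 0.5 | (0.5 − 0.25)/2 = 0.125 |
| 1/1/1 | 3/3 = 1 | 1 | 0 |

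**Second row in full.** Suppose each intervention alone reduces pain by 1 point at week 16. Then M = G = 1 + 1/2 = 1.5. Memantine without imagery is fitted as 1.5 − 0.25 = 1.25 (true 1.0), and with imagery as 1.5 + 0.25 = 1.75 (true 2.0). Combination versus double control is 1.5 + 1.5 = 3.0 (true 3.0).

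**Simulation check of that row.** In 150 trials with N = 204, correlation decaying with time, and 5%, 8% and 10% missing at weeks 16, 26 and 52, the means were: interaction 0.51; memantine without imagery 1.25; memantine with imagery 1.76; combination versus double control 2.98; marginal memantine 1.51.

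**After adding the three-way term.** In the noise-free calculation for the same row, every week-16 quantity is recovered exactly.

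**Precision at N = 182, adjusted for baseline.** The week-16 interaction has SE 4 × 2 × √(1 − 0.7²)/√182 = 0.42. Held constant over time, its SE is 0.33 under exchangeable correlation and 0.416 under decaying correlation. The ratios are 0.4235/0.3302 = 1.28 and 0.4235/0.4160 = 1.02. The SE of a conditional effect is 0.30 with the three-way term and 0.27 to 0.30 without it.

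**Effect on the check.** For 1/0/0 under exchangeable correlation, with z = 2.24, the constant-interaction model is expected to show 0.33 ± 2.24 × 0.3302, about −0.41 to 1.07. The week-16 term would show 1.00 ± 2.24 × 0.4235, about 0.05 to 1.95.

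**The case against.** - **The interaction may be small or stable.** The Trial design section sees little reason to expect one, and a constant interaction gives no bias. Nothing in the document shows an interaction that is present at week 16 and gone by week 26. The memantine schedule is 4 weeks of titration, 8 of maintenance and 4 of taper, and pain is rated over the previous 7 days, so week 16 falls at the end of the taper and need not be where an interaction peaks. This stands: the size is conditional, and the 1/0/0 row is an extreme case.
- **Pooling may be a fair trade.** For 0.5/0.25/0 under exchangeable correlation, the root mean squared error of the interaction is √(0.25² + 0.33²) = 0.41 pooled, against 0.42 with the three-way term. That is a tie. Under decaying correlation it is √(0.25² + 0.416²) = 0.49 against 0.42, and for 1/0/0 under exchangeable correlation it is √(0.67² + 0.33²) = 0.75 against 0.42. So the objection stands only for a modest interaction under exchangeable correlation.
- **The multi-arm contrasts may come from another model.** The section ties margins to the conditional effects and names no model for the comparisons with double control. A reader might infer that the statement on unbiasedness contradicts the model. The document does not establish this: the sentence is a general one with a citation, and a separate four-arm fit would satisfy it.
- **Only supportive analyses are touched.** This stands. Table 2 defines marginal estimands, and the General analysis principles section disclaims statements about statistical significance.

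**Conclusion.** The point holds as a defect of the sensitivity analyses. As listed, the model yields one interaction pooled over 16, 26 and 52 weeks, while the assumption it is meant to check matters at week 16. The interaction is off by Ibar − I16 and the conditional effects by half that amount. In the three fading scenarios the conditional error is 0.125 to 0.33 NRS points, against a 1-point target difference. These sizes rest on assumed interactions and on balanced data.

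Three stronger readings are tempting and not supported:

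- That the week-16 conditional and single-intervention effects are themselves averages over the three timepoints. They combine a week-16 marginal effect with half the averaged interaction, so they carry only half its error.
- That all multi-arm contrasts are biased. Combination versus double control is not, under balance; memantine-only and imagery-only versus double control are off by the same half only if they come from this model.
- That the primary results are at risk. The marginal week-16 effects are unaffected under balance.

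The change is still worth making, because a check on an assumption should work when the assumption fails, and the remedy is cheap.

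**What to change.** Add the memantine × graded motor imagery × time interaction, either to the main model or at least to the model used under Sensitivity analyses. State there that the interaction, the conditional effects and the comparisons with double control are reported at week 16 from that model. Naming the model for the multi-arm contrasts also settles what the statement on unbiasedness refers to.

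The cost is two further parameters and a sentence of text. The interaction's standard error rises by about 2% (correlation decaying with time) to 28% (exchangeable correlation); that of a conditional effect rises from 0.27–0.30 to 0.30 NRS points. The primary marginal estimate is unchanged under balance. Final assessment is expected in Q2 2027, so the wording can be settled before the true allocations are analysed.
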